## Abstract

**Introduction:**

Post-stroke fatigue (PSF) is highly prevalent and lacks of effective management. Recent evidence suggest the use of transcranial direct current stimulation (tDCS) to reduce PSF. However, the effect was not lasting and the working mechanisms was unclear. The purpose of this study is to determine the behavioral and neurophysiological effects of five daily sessions of tDCS on PSF.

**Methods and analysis:**

This will be a double-blind randomized controlled trial targeting an enrollment of 32 participants with subacute-chronic stroke and significant fatigue (average Fatigue Severity Scale (FSS) > 4). Participants will be equally randomized to either anodal tDCS or sham tDCS groups. The anodal tDCS group will receive 20 minutes of 2-mA anodal tDCS applied to the ipsilesional primary motor cortex (M1) for five consecutive days. The sham tDCS group will receive the same protocol except there will be no active current delivered. Outcome assessments will take place at baseline (prior to randomization), immediately after the intervention, and at one-month follow-up. The primary behavioral outcome will be the FSS and the primary neurophysiological outcome will be an input-output curve of motor cortex excitability derived using transcranial magnetic stimulation. Secondary behavioral outcomes will include Fatigue Scale for Motor and Cognitive Function, Visual Analog Scale-Fatigue, Borg Rating of Perceived Exertion, and Paas Mental Effort Rating Scale. Secondary neurophysiological outcome will be the functional connectivity of the fronto-striato-thalamic network acquired using resting state functional Magnetic Resonance Imaging (MRI). Repeated measure ANOVA or ANCOVA will be conducted for all outcomes to compare the change between groups.

**Discussion:**

Little is known about effective treatments for PSF and the underlying mechanisms of PSF. tDCS is a promising tool to provide targeted intervention to reduce PSF symptoms. However, its lasting effect and working mechanism on PSF is elusive. The results of this clinical trial will offer critical information for PSF management and investigation.

**Trial registration:**

This trial was registered in February 1 2024 with ClinicalTrials.gov under the registration number NCT06088914.

## Introduction

Post-stroke fatigue (PSF), defined as intensified perceived effort during activities, is one of the most common complications after stroke with a prevalence as high as 65% [1]. In contrast to fatigue experienced by healthy individuals, PSF is chronic, disproportional to the intensity of activity, and does not always alleviate with rest [2,3]. PSF limits participation in rehabilitation and physical activities, consequently leading to less than optimal stroke recovery and reduced quality of life [4,5]. Given its high prevalence and significance, management of PSF has been identified as a top priority for stroke care and research [6–8].

To date, several pharmacological, physical, and psychological approaches have been examined for PSF management; however, few have demonstrated satisfactory effectiveness [9–12]. Similar to pathological fatigue in other populations, PSF is associated with increased perceived effort during activities [13–16] and altered neuroplasticity including reduced cortical excitability [17–19] and altered structural and functional connectivity [20–22]. Specifically, multiple studies have shown that reduced ipsilesional primary motor cortex (M1) excitability assessed using transcranial magnetic stimulation (TMS) is related to PSF [17–19,23,24]. This observation has motivated the use of non-invasive brain stimulation to modulate cortical excitability with the goal to improve PSF [25–30]. Transcranial direct-current stimulation (tDCS) is a widely used non-invasive brain stimulation technique that modulates cortical excitability. Anodal tDCS increases cortical excitability and cathodal tDCS has the opposite effect [31]. Previous tDCS studies have supported its efficacy in motor and cognitive recovery after stroke [32,33]; however, its use for PSF has only been recently explored. A study conducted by De Doncker et al. reported that a single session of anodal tDCS over ipsilesional M1 improved PSF as measured by the Fatigue Severity Scale (FSS) 1 week post-intervention [27]. However, the positive effect did not persist to the 1-month follow-up and no correlation was found between changes in brain excitability and changes in the FSS score. Other studies have investigated the effects of anodal tDCS to left dorsolateral prefrontal cortex on PSF but the results were equivocal and the mechanism unclear [25,26]. Therefore, while tDCS holds promise as a treatment for PSF, the working mechanism of its therapeutic effects is largely unknown.

Studies have suggested that PSF involves neural networks beyond M1 [20–22]. A pharmacological trial showed that functional connectivity of the fronto-striato-thalamic network predicted Modafinil induced PSF reduction [34]. Fronto-striato-thalamic network has been implicated in other pathological fatigue [35–37] and is likely to play a role in PSF [38]. Further, because the fronto-striato-thalamic network is anatomically and functionally connected to M1, altered M1 excitability after stroke is likely related to connectivity in this network [39,40]. Therefore, tDCS applied to M1, in addition to changing M1 excitability, might also modulate the fronto-striato-thalamic network and result in reduced PSF. Examining both brain excitability and connectivity might shed light on the underlying mechanism of PSF and the working mechanism of tDCS on PSF.

The purpose of this double-blind, randomized controlled trial is to investigate the effects of multiple sessions of anodal tDCS to ipsilesional M1 on PSF and underlying neurophysiology. We hypothesize that compared to the sham group, the anodal tDCS group will show a greater decrease in fatigue and the effect will last up to 1 month (Aim 1). We also hypothesize that compared to sham tDCS, anodal tDCS will significantly increase ipsilesional M1 excitability and the functional connectivity between ipsilesional M1 and the fronto-striato-thalamic network (Aim 2). Lastly, we hypothesize that individuals who show a greater change in the neurophysiological outcomes (M1 excitability, brain connectivity) will demonstrate a greater reduction in fatigue (Aim 3).

## Materials and methods

### Study design and setting

The study is ongoing and we anticipate that participant recruitment will be completed in May 2026, data collection to be completed in July 2026, and resulted are expected in October 2026. This study is a two-arm double-blind randomized controlled trial. Eligible participants will be randomized to either anodal or sham tDCS groups and measurements will be taken at baseline, post-intervention, and one-month follow up. To facilitate recruitment and retention, participants will be given the option to receive five additional sessions of tDCS after the follow-up assessment in which all participants will receive anodal tDCS. The trial adheres the SPIRIT schedule (Fig 1) and will be reported using the CONSORT guidelines (Fig 2). The study will be conducted in a university-based laboratory. This trial is registered on Clinicaltrials.gov (NCT06088914).

**Fig 1 pone.0324591.g001:**
[figure not shown]
Schedule of enrollment, interventions and assessments.

**Fig 2 pone.0324591.g002:**
[figure not shown]
Consort flow diagram of enrollment, intervention and assessment.

### Participants

The inclusion criteria are: at least 18 years old; have a history of unilateral stroke ≥ 3 months prior to enrollment; have an average score ≥ 4 on the FSS [41]; have some movement capability in the more affected arm (Fugl Meyer Upper Extremity [42] ≥ 28) to ensure ability to perform the reaching task; and be able to follow three-step commands. Exclusion criteria are: acute medical problems; presence of any contraindication to tDCS, MRI or TMS; significant pain that interferes with arm movements; use of medication which may affect the level of fatigue; and presence of significant depression (Patient Health Questionnaire-9 > 10) [43].

### Sample size estimation

Previous tDCS studies on pathological fatigue reported medium-large effect sizes (f > 0.35) [25,27,57,58]. A *prior* power analysis (G*Power version 3.1.9) using a more conservative effect size (f = 0.25), a power of 0.80, α-level at 0.05, and a correlation among the repeated measures of 0.5 indicate that a minimum of 28 participants is required for repeated measures analysis of variance (ANOVA). With consideration of a 10% attrition rate, a sample size of 32 (N = 16 per group) will be required.

### Recruitment

This is a single-site study with a target enrollment of two participants per month, totaling 32 participants over 18 months. The study site is located within a medical strict in a metropolitan area. The research team has established partnership with the clinical sites within the district. Further, the study site houses a stroke center which will serve as a primary referral source. Collaborating physicians and therapists will refer patients to enroll in our study. Additional recruitment effort include posting on social media (e.g., Facebook) and printed flyers in different clinics. Financial compensation will be provided upon study completion to enhance recruitment. The start date of the recruitment period for this study was 15/12/2023.

### Randomization and blinding

Eligible participants will be randomized into either the anodal or sham tDCS group using a blocked randomization procedure. The blocked randomization will create groups that have equal numbers of females because sex is a determinant of PSF [44,45]. The study biostatistician who is not involved in intervention or assessments will assign the participants and prepare concealed envelopes with group allocation. The concealed envelopes will be given to the interventionists who will provide tDCS intervention but will not participate in the assessments. Participants and outcome assessors will be blinded to group assignment.

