### Data management and data analysis

Clinical and behavioral data will be collected via paper-based questionnaires and entered into the online Research Electronic Data Capture (REDCap) hosted at the Texas Woman’s University. All paper-based files will be coded and stored in a locked cabinet with files consisting of identifiable information (e.g. informed consent) kept separate from the clinical data. Kinematic data and neurophysiological data will be in electronic format. All electronic data will be stored on password-protected university servers. All data will be coded to ensure participant confidentiality throughout the study. The statistician and the principal investigator will review the data every three months to ensure completeness and data quality. The final de-identified dataset will be deposited to NICHD DASH for public access upon the completion of publications.

All data analyses will be performed in SPSS v28 (SPSS Inc., IBM, USA) by the biostatistician and significance will be set at p < .05. The percentages and patterns of missing data will be assessed to determine if pairwise deletion will be used for analysis or if an intention-to-treat strategy needs to be applied to replace missing values [57]. Comparison of baseline variables between groups will be conducted. If a baseline difference exists and judged to be a potential confound (e.g. baseline FSS score), the variable will be included as covariate in the primary analyses. Normality and outliers will then be checked to see if parametric analysis assumptions are met.

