To examine effects on clinical, behavioral, and neurophysiological outcomes, we will perform a 2 group (anodal, sham) x 3 time point (baseline, post-intervention, follow-up) repeated measure ANOVA/ANCOVA. Resting state functional MRI data will be analyzed with a 2 group x 2 time point (baseline, post-intervention) ANOVA/ANCOVA. Post-hoc Bonferroni-adjusted comparisons will be completed if a main effect or interaction is detected. To examine whether individuals who show a greater change in neurophysiological outcomes demonstrate a greater reduction in PSF, Pearson or Spearman correlational analyses will be run to examine the relationship between changes in neurophysiological measures (input-output curve, fronto-striato-thalamic network connectivity) and changes in PSF (FSS). The strength of relationships will be interpreted as follows: r < 0.25 = little or no relationship; r of 0.25 to 0.5 = fair; r of 0.5 to 0.75 = moderate; and r > 0.7 = strong relationship [58].

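### Sex is balanced by the randomisation but is absent from the planned models, and the stated covariate rule will in practice not bring it in (low severity: precision, not validity)

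*Protocol article*

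**What the plan says.** The Randomization and blinding section of the protocol article states: "The blocked randomization will create groups that have equal numbers of females because sex is a determinant of PSF". Sex is the only factor on which allocation is constrained.

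The analysis is set out under Data management and data analysis. For clinical, behavioural and neurophysiological outcomes, "we will perform a 2 group (anodal, sham) x 3 time point (baseline, post-intervention, follow-up) repeated measure ANOVA/ANCOVA". For imaging, "Resting state functional MRI data will be analyzed with a 2 group x 2 time point (baseline, post-intervention) ANOVA/ANCOVA". Neither model has a sex term, and the ANCOVA option names no covariate.

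The same section gives one rule for adding a covariate to the main models: "If a baseline difference exists and judged to be a potential confound (e.g. baseline FSS score), the variable will be included as covariate". It does not define a baseline difference by any test or threshold. The general criterion is "significance will be set at p < .05". Post-hoc comparisons follow if either a main effect or an interaction is detected.

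**The concern.** The randomisation section treats sex as prognostic for fatigue and forces the arms to match on it. The covariate rule then looks for variables on which the arms fail to match. Read together, the two sections screen out the one factor that the protocol itself names as a determinant of the condition under study.

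When allocation is balanced on a prognostic factor, that factor no longer contributes to chance differences between the arms. If the model ignores it, its variance stays in the error term of any test on which it acts. The standard error is then larger than the design warrants, and the test is conservative. What is at stake is precision in a small trial, with 28 participants needed for analysis and 32 enrolled.

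**Working it through.** **1. The plan's own sample size.** Inputs from Sample size estimation: "using a more conservative effect size (f = 0.25), a power of 0.80, α-level at 0.05" and "a correlation among the repeated measures of 0.5". There are k = 2 groups and m = 3 time points. For the group x time interaction:

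- noncentrality = N f² m / (1 − ρ) = 28 × 0.0625 × 3 / 0.5 = 10.5
- df = (k − 1)(m − 1) = 2 and (N − k)(m − 1) = 52
- power = 0.812

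This agrees with the statement that "a minimum of 28 participants is required for repeated measures analysis of variance (ANOVA". Then 28 / 0.9 = 31.1, which rounds up to 32. Both stated figures reproduce. The between-group variant would need 86, so 28 does not rest on that test.

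**2. Can the covariate rule select sex?** The article gives neither the block size nor the proportion of women, and does not define a baseline difference. Assumptions: permuted blocks of 2, 4 or 6 within sex; 30% or 50% female; N = 32; a difference means p < .05 by chi-square or Fisher test; 10,000 simulated allocations per case.

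| Block size | Largest difference in number of females | Chance of p < .05 |
|---|---|---|
| 2 | 1 | 0 |
| 4 | 2 | 0 |
| 6 | 3 | 0 |

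The results were the same for both proportions and both tests. With 16 per arm, chi-square significance needs a split such as 7 v 1, 8 v 2, 9 v 3 or 11 v 5 females.

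**3. Which tests does omission affect?** Setting: N = 28, 14 per arm, 7 women in each, unit variance, correlation 0.5.

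*Sex shifts the FSS level by a constant.* The group x time test uses contrasts over time that sum to zero, so a constant shift drops out. The between-group test uses each participant's mean over three visits:

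- residual variance of that mean = (1 + 2 × 0.5) / 3 = 0.667
- a 1 SD sex effect with half the sample female adds 1² × 0.25 = 0.25
- the error variance is inflated by 0.917 / 0.667 = 1.375, and the standard error by √1.375 = 1.17

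*Sex shifts both post-baseline visits by d SD.* The pattern (0, d, d) has squared length 2d² − (2d)²/3 = 2d²/3 after its mean is removed. Multiplying by 0.25 and spreading over two contrasts adds d²/12 to a contrast variance of 1 − 0.5 = 0.5. The inflation is 1 + d²/6:

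- d = 0.5: 1.042; noncentrality 10.5 / 1.042 = 10.1
- d = 0.8: 1.107; noncentrality 10.5 / 1.107 = 9.5
- d = 1.2: 1.24; noncentrality 10.5 / 1.24 = 8.5

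**4. Simulation under the planned model** (6,000 trials per case, interaction effect f = 0.25):

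| Assumed sex effect | Group x time power, without → with sex | Group x time type I error, without → with sex |
|---|---|---|
| None | 0.819 → 0.817 | 0.049 → 0.049 |
| 1 SD on level only | 0.805 → 0.804 | 0.050 → 0.050 |
| 0.5 SD on change | 0.796 → 0.812 | 0.047 → 0.053 |
| 0.8 SD on change | 0.779 → 0.818 | 0.039 → 0.052 |
| 1.2 SD on change | 0.720 → 0.811 | 0.026 → 0.051 |

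For the between-group main effect, type I error without → with sex was 0.040 → 0.047 for a 0.5 SD level effect and 0.020 → 0.044 for a 1 SD level effect.

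**The case against.** The strongest objection is that the main hypothesis is safe. It concerns a greater decrease in fatigue, which is the group x time interaction. The article calls sex a determinant of post-stroke fatigue and says nothing about sex predicting change after real or sham stimulation. A difference in level cancels from the interaction test, and adding sex then gains nothing (0.805 v 0.804). This stands, and it limits the point.

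A reader might infer that the precision gained from sex-balanced allocation is thrown away, or that the primary test is materially conservative. The documents do not support that: it would need a sex effect on change, for which they give no evidence or size. Nor can one say that reported confidence intervals will fail to match the randomisation, because the analysis section does not mention confidence intervals.

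A second objection is that the covariate rule says when a variable will enter and does not bar others, and that an analysis plan not shown could name sex. That is fair as far as it goes. A rule based purely on judgement could also admit sex, although a gap of 0 to 3 women gives little ground for it. But the article states a positive rule that pulls against its own reason for balancing, and an analysis plan that followed the rule as written would leave sex out. This is more than a detail left to another document.

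A third objection is that the group main effect is not the hypothesis of interest. That is true, but the plan also lets a main effect trigger post-hoc comparisons, so its error rate is not irrelevant.

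**Conclusion.** The point holds as a low-severity matter of precision. The plan balances on sex, models only group and time, and states a covariate rule that will in practice not select a factor balanced by design. Omission gives no bias and no type I inflation; any error is on the conservative side.

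The main-effect test is conservative if sex affects FSS level, with type I error about 0.02 for 1 SD. Power for the key interaction test falls only if sex predicts change, and the 9-point loss needs an effect as large as 1.2 SD. These sizes are assumed, as are the block sizes and the p < .05 reading of a baseline difference. The sample size of 28 analysed and 32 enrolled is reproduced and unaffected.

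**What to change.** State in the analysis section that sex, as the balancing factor in the randomisation, enters as a prespecified fixed factor with its time interaction, whatever the observed baseline balance. Apply this to the primary FSS model and to the other fatigue outcomes. The article links sex only to fatigue, so its own rationale does not call for the term in the TMS or imaging models.

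The cost is one sentence. At N = 28 the error degrees of freedom fall from 26 to 25 for the between-group test and from 52 to 50 for the interaction. If sex has no effect, power is essentially unchanged (0.819 v 0.817). No new data are needed and N does not change. The article describes the study as ongoing with no interim analysis planned, so the change can be made before the group comparison is seen.

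### The biostatistician who makes the allocation also runs all analyses under look-then-decide rules, so the 5% error level is left unprotected

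*Protocol article*

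**What the plan says.** On allocation and blinding, the protocol article (Randomization and blinding) states: "The study biostatistician who is not involved in intervention or assessments will assign the participants and prepare concealed envelopes with group allocation". The same section lists who is masked: "Participants and outcome assessors will be blinded to group assignment". The analyst is not on that list.

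On analysis, the section Data management and data analysis states: "All data analyses will be performed in SPSS v28 (SPSS Inc., IBM, USA) by the biostatistician". It then leaves three choices until the data are in:

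- **Missing values:** "The percentages and patterns of missing data will be assessed to determine if pairwise deletion will be used for analysis", the alternative being replacement under an intention-to-treat strategy.
- **Covariates:** "If a baseline difference exists and judged to be a potential confound (e.g. baseline FSS score), the variable will be included as covariate". No threshold is given, and the text does not say who decides.
- **Outliers and distribution:** "Normality and outliers will then be checked to see if parametric analysis assumptions are met". No cut-off or consequence is stated.

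The model is given as a two-group by three-time-point repeated measures ANOVA or ANCOVA. On review of accumulating data the section says: "The statistician and the principal investigator will review the data every three months to ensure completeness and data quality". Ethics and monitoring adds that no interim analysis is planned.

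**The concern.** The protocol sets out a procedure in which the data are inspected first and the analysis is chosen afterwards. The covariate rule cannot be applied at all without comparing the arms. On the natural reading, the person carrying out that procedure is the one who made the allocation.

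The primary behavioural outcome is a self-reported fatigue score in 32 people. In a trial of that size, dropping or replacing a few values, or adding a covariate, can move a p-value across 0.05. If such choices are made with results by arm in view, even without intent, the estimate can be biased and the nominal 5% no longer describes the chance of a false positive. Masking participants and assessors protects how the outcome is measured. It does not protect how the outcome is analysed.

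**Working it through.** **1. The plan's own figure.** Inputs from Sample size estimation: f = 0.25, power 0.80, alpha 0.05, correlation 0.5, with k = 2 groups and m = 3 time points. For the repeated measures interaction:

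- lambda = f² × N × m / (1 − rho) = 0.0625 × 28 × 3 / 0.5 = 10.5
- df1 = (k − 1)(m − 1) = 2
- df2 = (N − k)(m − 1) = 26 × 2 = 52

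Power is 0.812, so 28 reproduces. With 10% attrition, 28 / 0.9 = 31.1, which rounds up to 32, or 16 per arm. The sample size is not in dispute.

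**2. Who does what.** Allocation belongs to the study biostatistician (Randomization and blinding). Analysis belongs to the biostatistician and the quarterly data review to the statistician (both Data management and data analysis). That these are one person is the natural reading, but it is not stated outright.

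**3. What the open choices could do to the error rate.** Trials were simulated with no treatment effect: 16 per arm, three visits, normal data, correlation 0.5. Several inputs are assumptions that the document does not give:

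- 10% of participants have missing values, completely at random.
- Deletion is modelled as dropping those participants.
- Replacement is last observation carried forward.
- An outlier is a change score beyond 2 SD.
- ANCOVA is the group effect on the mean of the two post-baseline values, adjusted for baseline.

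The error rate is the share of null trials in which the smallest p-value among the available analyses is below 0.05.

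| Analyses available | Type I error |
|---|---|
| One, fixed in advance (any of the eight variants) | 5.0% to 5.3% |
| Mechanical rule: ANCOVA only if baseline p < 0.05 | 4.7% |
| Best of deletion or replacement | 6.0% |
| Best of outliers kept or removed | 7.6% |
| Best of ANOVA or ANCOVA | 8.5% |
| Best of four: ANOVA/ANCOVA by deletion/replacement | 10.2% |
| Best of all eight, adding outliers kept/removed | 15.0% |

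These come from 20,000 trials, with a Monte Carlo error of about 0.2 to 0.3 points. Separate runs gave 10.7% and about 11% for the four-analysis case and about 14% for the eight-analysis case.

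**4. Applying the plan's own condition.** The table's best-of rows treat ANCOVA as always available, whereas the plan allows a covariate only after a baseline difference. A further 12,000 null trials made ANCOVA optional only when the baseline comparison gave p below an assumed threshold, again keeping the smallest p over deletion and replacement:

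- threshold 0.05: 6.7%
- threshold 0.10: 6.8%
- threshold 0.20: 7.2%

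Adding the assumed 2 SD outlier choice raises this to about 9% to 10%.

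**5. What masking alone would do.** The p-value of the F test is the same whichever label is anodal, so analysing under fixed A/B labels leaves the selection problem where it was. Removing the arm column also does not mask the person who made the list. The protection has to come from fixing the rules.

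**The case against.** The strongest counter-argument is that this is a condensed journal article and that a separate analysis plan may exist. Analyst masking, dated decision locks and outlier rules commonly sit there, and their absence here is not in itself a fault. The article claims masking only for participants and assessors, so nothing is contradicted. That much stands. It does not answer the text that is present, which directs that the analysis be chosen after the data, including differences between arms, have been examined.

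A reader might also infer more than the documents support:

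- **That the error rate is inflated.** The documents do not show this. A mechanical rule keeps it at 4.7%, and holding the list changes nothing on its own. Inflation requires selection among results.
- **That the quarterly reviews add to the error.** Their stated purpose is completeness and quality, no interim analysis is planned, and nothing says data are shown by arm. They give access to data; they are not a further test.
- **That the biostatistician makes every choice.** The text names no judge of confounding, so this is a close inference only.
- **That the error is larger still if sex may be put in or left out.** Randomization is meant to give the arms equal numbers of females, so sex is the variable least likely to meet the plan's baseline-difference condition.

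**Conclusion.** The concern holds as a lack of protection, not as a demonstrated inflation. The protocol as written gives one role both the allocation and the analysis, and leaves missing-data, covariate and outlier decisions until after the data are seen.

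The size is an upper bound, reached only if the most favourable result is always kept: roughly 7% to 10% within the plan's baseline-difference condition, and roughly 11% to 15% if ANCOVA is treated as freely available, against "by the biostatistician and significance will be set at p < .05". In each range the lower figure excludes outlier handling and the upper includes it. Both rest on the assumed missingness, replacement method and 2 SD cut, none of which is fixed by the document. An unseen analysis plan may narrow the choices. The point deserves action because the remedy is cheap. Study design and setting expects data collection to end in July 2026, so a lock can still precede any look at results by arm, provided none has yet been taken.

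**What to change.** Replace the look-then-decide paragraph in Data management and data analysis now with:

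- **A prespecified covariate set**, for example baseline FSS and sex, used whatever imbalance is observed. The present rule must be replaced, not merely postponed, because it compares groups and cannot be applied with the arm withheld. If baseline FSS is chosen, state whether baseline also stays as a time point, since it would then be both covariate and outcome.
- **One named missing-data method.**
- **One outlier and normality rule**, with its cut-off and its consequence.

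Make any remaining decision on pooled data without the arm variable, date it, and lock the SPSS syntax before the allocation is merged. State that the three-monthly reviews show no outcome data by arm.

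The cost is a paragraph of wording and one dated step, with no extra staff or patients. Locking the rules leaves the planned 32 unchanged; the sample size was not recalculated for a covariate-adjusted model. The downside is that the analysis can no longer be adapted after unblinding.
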